## Abstract

The workplace is a major contributor to excessive sitting in office workers. There are a wide array of adverse effects of high volumes of sitting time, including an increased risk of type 2 diabetes and depression. Active workstations can be used in effective interventions to decrease workplace sitting. However, there are a lack of interventions that have been developed using a systematic process that is informed by participant needs and a framework for identifying the most appropriate content for the intervention. Applying these methods could increase adherence and potential effectiveness of the intervention. Therefore, the purpose of this pilot study is to examine the feasibility, acceptability, and efficacy of a tailored workplace intervention to reduce and break up sitting in office workers that has been developed using the Behavior Change Wheel and the APEASE (Acceptability, Practicability, Effectiveness/cost-effectiveness, Affordability, Safety/side-effects, Equity) criteria. This article reports the protocol for this study that is currently ongoing. Participants will be cluster-randomized (by offices) to control and intervention groups. The evaluation of the intervention includes determining feasibility by assessing participant recruitment, retention and data completion rates. Adherence to the intervention will be assessed based on daily sitting and standing time relative to guidelines provided to participants as part of the intervention. Outcome measures also include productivity measured using Ecological Momentary Assessment, absenteeism, presenteeism, cardiometabolic risk markers, and wellbeing. The findings of this study will inform the effective design and implementation of interventions for reducing and breaking up sitting in office workers.

## Introduction

Sedentary behavior has been described as any waking behavior in a sitting, reclining or lying posture that has an energy expenditure of ≤ 1.5 metabolic equivalents (METs) (1). In the United Kingdom, high levels of sedentary behavior have been reported with male and female employees sitting more than 11 h/day on average (2). Studies have identified the workplace as a major contributor to excessive sitting (3) with one study reporting that office workers spent 79% of their working day sitting and 42% of their work hours engaging in prolonged sitting (i.e., sitting bouts ≥ 30 min) (4).

Individuals who spend prolonged periods being sedentary have an increased risk of adverse health outcomes, including type 2 diabetes, cardiovascular disease, some cancers, and mental health problems such as depression and anxiety (5–9). This has led to incorporating a focus on reducing and breaking up sedentary behavior in national and international physical activity guidelines (10, 11). As high amounts of sitting are accumulated in the office workplace, this is a key setting where interventions could be implemented to improve occupational and public health. Indeed, an expert consensus statement recommended that workers who are in predominantly desk-based occupations should start by accumulating 2 h of standing and light activity during working hours each day, and progress to reaching a target of 4 h per day (12).

There is a growing body of evidence that suggests height-adjustable workstations (i.e., a workstation that permits the user to interchangeably work in a seated or standing posture) could be effective for decreasing sitting in the workplace (13). When height-adjustable workstations are provided as part of multi-component interventions that also include strategies such as education, manager support, standing meetings, self-monitoring and social support, workplace sitting has been significantly reduced by 45 to 83 min/work shift after 12 months (14, 15). Although these interventions appear promising, management of organizations might be reluctant to implement them if productivity is negatively affected (16). With respect to productivity concerns, a systematic review reported that productivity is likely to be unaffected by using a height-adjustable workstation (17). There are also limited studies that have reported taking employee's perceptions and experiences into account when developing interventions to reduce workplace sitting (18), which may limit intervention adherence and effectiveness. By involving the target audience in the development of interventions, this will help to ensure their needs are met and enhance their adherence and engagement (19). The Behavior Change Wheel (BCW) (20, 21) has been recommended for guiding the systematic process of developing an intervention using a framework that takes into account the needs of the target audience. To the author's knowledge, only one previous office workplace intervention has been developed using the BCW (18); the SMArT Work intervention in National Health Service employees led to significant reductions in sitting at work and improvements in job performance, work engagement, occupational fatigue, sickness presenteeism, anxiety and quality of life over 12 months (15). Further research is required in other occupational groups to strengthen the evidence base for incorporating a focus on reducing and breaking up sitting in workplace policy and practice. Demonstrating the effectiveness of such interventions for improving work-related outcomes, such as worker productivity, will be important for encouraging the adoption of such changes in policy and practice. The use of ecological momentary assessment (EMA) facilitated through smartphone technology provides the opportunity to collect simultaneous time-stamped data with limited recall bias to elucidate on the temporal effects of posture and activities on work performance throughout the workday (22, 23). However, the effects of workplace sitting interventions on EMA measures of work-related outcomes is limited.

This article describes the protocol for a pilot cluster-randomized controlled trial (RCT) to evaluate the feasibility and efficacy of a multi-component intervention to reduce and break up workplace sitting, including the systematic process for identifying the content of the intervention using the BCW. The effects of the intervention on a range of sitting, activity, health, wellbeing and work-related outcomes (including EMA assessment) will be evaluated.

## Methods

### Study Design and Overview

The study adopts an 8-week, two-arm cluster RCT design that is planned to be conducted during Spring and Summer months (see Figure 1 for overview of study design). The unit of randomization will be the workers' offices in line with previous research (24). Participants will be randomly allocated into clusters with each cluster being in either the control or intervention group for a period of 8 weeks. Given the nature of the intervention, blinding from participants or the core research team is not possible.

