### Randomization

To minimize contamination between groups in open plan offices, a cluster randomization approach will be used with offices being the unit of randomization i.e., randomization into either the intervention or control group will be assigned on an office basis (28). The number of clusters is projected to be approximately eight with an average cluster size of six (29). Randomization will be achieved by assigning a cluster ID to each office and clusters then being allocated to intervention or control group using an online randomization tool (https://www.randomlists.com/team-generator) by an independent researcher (30). Randomization will take place before the collection of baseline measurements and group allocation will not be disclosed to participants until the completion of baseline assessment (28).

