#### Primary Outcome Measure: Workplace Sitting Time

The primary outcome measure is sitting time at work, which will be measured using an activPAL3 activity monitor (PAL Technologies Ltd., Glasgow, UK). The activPAL is a portable lightweight device, which is usually worn on the front of the mid-thigh to take measurement of postural information by recognizing periods of lying down/sitting, standing, and stepping based on the inclination of the thigh (39, 40). The activPAL has high reliability and validity for assessing sitting, standing and stepping (41). In this study, the device will be worn on the right thigh for seven full consecutive days (42) at baseline and during the last week of the intervention. The device will be waterproofed by wrapping it within a nitrile sleeve and an adhesive medical dressing. In addition, participants will complete a diary to keep record of their waking time, working hours and time they go to bed while wearing the device to enable calculation of waking and working time wear periods (42). Data from the activPAL will be considered valid only if the device is worn for a minimum of 75% of the workplace monitoring time (39, 40). The sitting time at work variable will be normalized by expressing it as a percentage of the duration of the working day for each participant.

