#### Secondary Outcome Measures

##### Sitting, Standing and Stepping

In addition to workplace sitting, the activPAL will be used to measure total daily sitting time and the following variables for working hours and across the waking day: time spent in sitting bouts <30 min and ≥30 min, the number of sitting bouts <30 min and ≥30 min, standing time, number of sit-to-upright transitions, number steps and stepping time. Processing PAL (v1.1, University of Leicester, Leicester, UK) will be used to process the data. A validated algorithm (43) will be used to identify valid waking wear data with heat maps being generated to visually check classifications of waking wear time against information provided in the participant's diaries. Waking bout corrections will be made where errors are identified (42). A valid day for daily data will be accepted if wear time is ≥10 h per day; ≥500 steps per day and if not recording > 95% data in one activity category (i.e., sitting, standing or stepping). The resulting data for all primary and secondary activPAL outcome measures will be averaged across all valid days. All time variables for the working day will be normalized by expressing them as a percentage of the work shift duration. All count variables, such as the number of sitting bouts, will be normalized by expressing them as counts per hour.

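### The article rules out blinding the whole core team, yet the visual correction of activPAL wear data could be masked and no masking is provided for

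*Protocol article*

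**What the plan says.** The article's only statement on blinding is in Study Design and Overview. Citing what the intervention is, it says that "blinding from participants or the core research team is not possible". It makes no exception for any task.

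The activPAL data are handled in three steps:

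- Under Primary Outcome Measure, "The primary outcome measure is sitting time at work, which will be measured using an activPAL3 activity monitor". Participants keep a diary of waking time, working hours and bedtime "to enable calculation of waking and working time wear periods". Workplace data count only if the monitor is worn for at least 75% of the workplace monitoring time.
- Under Sitting, Standing and Stepping, a validated algorithm "will be used to identify valid waking wear data".
- The same section then describes "heat maps being generated to visually check classifications of waking wear time against information provided in the participant's diaries", and adds: "Waking bout corrections will be made where errors are identified." It gives numerical criteria for a valid day (at least 10 h of wear, at least 500 steps, no more than 95% in one activity category). All primary and secondary activPAL outcomes are averaged over valid days.

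The article does not say who makes the visual check, or whether that person knows the arm. The Randomization section mentions one independent person, who performs the allocation "using an online randomization tool (https://www.randomlists.com/team-generator) by an independent researcher". Allocation is made before baseline measurement. Concealing it until baseline is complete is promised for participants only.

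**The concern.** The reason given for the lack of blinding is narrower than the statement it supports. People who receive a height-adjustable workstation, install it, or run the information session must know the arm. Someone who opens a recorded file under a coded identifier need not.

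This matters because processing is not fully automatic. Deciding whether a long still period is waking time, sleep or non-wear takes judgement. If the person deciding knows the arm, corrections may differ between arms without intent. The activPAL is the trial's only device-based measure of behaviour, and participants know their arm. At stake are waking-day sitting, standing and stepping, and less directly the primary outcome and the 2 h and 4 h adherence classes.

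Baseline is not clearly protected either. Allocation precedes baseline and concealment is stated for participants only, so baseline files could also be checked with the arm known. Baseline values enter the mixed models as a covariate.

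**Working it through.** No figure in the article tests this point, so the text is compared first and a range of sizes follows.

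**Text side by side**

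1. *Scope of the reason.* It applies to receiving and delivering the intervention. Processing of recorded files is a later desk task that it does not reach.
2. *Is there judgement in processing?* Yes. The algorithm runs first, but the check against diaries is visual and corrections follow from it. The article has numerical thresholds for valid days and none for when or how to correct.
3. *What can be edited?* Waking-wear classification and waking bouts. Nothing provides for recoding sitting as standing or stepping.
4. *Route to waking-day outcomes.* Direct. If *m* minutes coded as waking sitting become sleep or non-wear, that day's sitting total falls by *m* minutes. An edit can also move a day across the 10 h threshold, so that it is kept or dropped.
5. *Route to workplace sitting and adherence.* Indirect. The shift is bounded by diary hours, so a correction acts through wear within the shift, the 75% rule and which days are valid.

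**Illustration for workplace sitting**

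Inputs: 79% of the working day spent sitting (Introduction, from a cited study); a shift of 8 h = 480 min (assumption); *m* minutes a day of work sitting reclassified as non-wear (assumption, varied). Sitting time is 0.79 × 480 = 379.2 min.

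- Shift length kept as denominator: fall = *m* / 480.
- Denominator shrinks with wear: fall = 0.79 − (379.2 − *m*) / (480 − *m*).

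| *m* (min/day) | Fall, shift denominator | Fall, wear denominator |
|---|---|---|
| 5 | 5/480 = 1.0 points | 79 − 374.2/475 (78.8%) = 0.2 points |
| 15 | 15/480 = 3.1 points | 79 − 364.2/465 (78.3%) = 0.7 points |
| 30 | 30/480 = 6.3 points | 79 − 349.2/450 (77.6%) = 1.4 points |
| 60 | 60/480 = 12.5 points | 79 − 319.2/420 (76.0%) = 3.0 points |

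The article normalizes to the duration of the working day, which is closer to the middle column. The last column is the lower bound if non-wear is also taken out of the denominator.

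For scale, the Introduction cites reductions of 45 to 83 min per shift in earlier multi-component trials: 45/480 = 9.4 and 83/480 = 17.3 points.

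These falls apply to a day that is edited. With equal numbers of valid days per person, the bias in the arm comparison is roughly (share of days edited in one arm − share in the other) × fall. If the shares differ by 0.2 (assumption), 60-min edits give 0.2 × 3.0 = 0.6 to 0.2 × 12.5 = 2.5 points, and 5-min edits give about 0.04 to 0.2 points. Equal editing in both arms gives no bias in the difference on this approximation.

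**The case against.** The strongest reply is that the article names no operator for the heat-map check. It is a condensed account, and the full protocol may assign the work to someone masked. The correction step also cites a source, which may contain a rule. Both points stand as far as they go. A reader might infer that staff who know the arm do edit the data, and the documents do not say so. They support only that this may happen. The reply does not remove the point, because the article does more than stay silent: it says the core team cannot be blinded, for a reason that does not reach this task.

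A second reply is that the process is mostly automatic. This too is largely right. A validated algorithm comes first and only identified errors are corrected. A reader might picture posture being recoded by hand, or the primary outcome being edited directly. The text supports neither.

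Third, this is a pilot, and masking the processor would leave untouched the diaries kept by unblinded participants, which set the working hours. That is true and limits the gain. It does not justify leaving the judgement step open as well.

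Finally, masking is neither free nor complete. Files and diaries must be relabelled, frequent standing may suggest the arm, and dates make the time point hard to hide.

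**Conclusion.** The point holds in a limited form. The statement on blinding is wider than its reason, and a judgement step in activPAL processing is left without provision for masking. Arm-related corrections could bias waking-day sitting, standing and stepping directly, and workplace sitting and adherence classes indirectly.

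The size cannot be estimated, because the article gives neither the frequency nor the extent of corrections. Under the assumed 8 h shift and 79% sitting, small edits matter little: 5 min a day is at most 1.0 point on an edited day. Only large edits that differ systematically by arm would approach the effects cited in the Introduction. A reader might take the 12.5-point figure as the likely bias. It is the extreme of an assumed range, and nothing in the article suggests that edits of that size occur or that they would differ by arm.

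This is a safeguard worth adding to the handling of the primary device data. It is not evidence that the results will be biased.

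**What to change.** 1. In Study Design and Overview, limit the sentence to participants and the staff who deliver the intervention.
2. In Sitting, Standing and Stepping, state who makes the heat-map check. State also that activPAL files and diaries, from baseline and follow-up alike, are processed under neutral codes that hide arm and office, and time point where feasible.
3. State that corrections follow a rule written before processing starts. If the cited source supplies one, say so and specify it. Lock the corrected data before arm is linked. The independent researcher already used for allocation could hold the key.
4. Report the number of corrected files by arm, so that readers can judge whether editing differed.

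The change is wording plus modest relabelling. It alters no participant procedure, sample size or analysis model. The Abstract describes the study as ongoing; the change can apply to files not yet processed, and any already corrected can be rechecked under codes. Masking will be imperfect, since standing patterns may suggest the arm, and bias from diaries kept by unblinded participants will remain. Both are best stated as limitations.

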**Figure 1 F1:**
[figure not shown]
Overview of study design.

The study is registered on ClinicalTrials.gov (NCT03560544). Ethical approval for the procedures detailed below was obtained from the University of Bedfordshire Institute for Health Research Ethics Committee (lHREC836). Participants will provide written informed consent prior to any testing procedures and the study is being conducted in accordance with the Declaration of Helsinki.

### Study Setting

The study will be conducted with office workers employed across a university campus and a local council, both located in the East of England region, UK. Participants were recruited from one campus at the university and employees at the council worked within offices at a single site. Clusters of participants will be recruited from both organizations who will be randomly allocated to the intervention or control group i.e., there will be intervention and control clusters located at each organization.

### Participant Recruitment

Management approval will be sought and obtained for the recruitment of the employees, changes to the workplace environment, and for study testing and communications to take place during work time. The project will be advertised to staff as part of a workplace wellbeing programme via internal mail, staff meetings, information fliers in offices and other strategic places within the participating organizations.

### Eligibility Criteria

Participants will be full-time desk-based office employees between the ages of 18 and 60 years employed in any job type and from any ethnic background. Individuals will be excluded from the study if they are pregnant, have a history of musculoskeletal complaints, non-ambulatory, or have a planned holiday that would mean they would not be at work for more than 2 weeks during the 8-week intervention period.

### Sample Size

There is no standard procedure for determining the sample size for pilot studies as their main purpose is to obtain an estimate of the standard deviation that could be used to determine the likely effect size to inform a full trial (25). Thus, the proposed study will recruit a total of 44 participants in two groups of 18 allowing for an attrition rate of 20%. This is in line with sample size recommendations for pilot studies (26) and that used in a previous related pilot study of a workplace intervention to reduce sitting (27).

### Randomization

To minimize contamination between groups in open plan offices, a cluster randomization approach will be used with offices being the unit of randomization i.e., randomization into either the intervention or control group will be assigned on an office basis (28). The number of clusters is projected to be approximately eight with an average cluster size of six (29). Randomization will be achieved by assigning a cluster ID to each office and clusters then being allocated to intervention or control group using an online randomization tool (https://www.randomlists.com/team-generator) by an independent researcher (30). Randomization will take place before the collection of baseline measurements and group allocation will not be disclosed to participants until the completion of baseline assessment (28).

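### The protocol article says both arms will be present at each organisation, but describes no randomisation by organisation for about eight offices and has no organisation term in either mixed model

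*Protocol article*

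**What the plan says.** All references are to the protocol article.

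- **Study Setting.** The participants are "office workers employed across a university campus and a local council". The section then states as a feature of the design that "there will be intervention and control clusters located at each organization".
- **Randomization.** The unit is the office: "randomization into either the intervention or control group will be assigned on an office basis". On numbers: "The number of clusters is projected to be approximately eight with an average cluster size of six". On method, each office receives a cluster ID, with "clusters then being allocated to intervention or control group using an online randomization tool"; an independent researcher does this. No stratum, block, allocation ratio or separate run per organisation is mentioned.
- **Statistical Analysis.** The main mixed model has arm and time as fixed effects, participant and cluster as random effects, and the baseline value as covariate. The additional model for the momentary-assessment data replaces time with posture and otherwise has the same structure. Organisation appears in neither.
- **Timing and blinding.** "Randomization will take place before the collection of baseline measurements", and "group allocation will not be disclosed to participants until the completion of baseline assessment". Under Study Design and Overview, "blinding from participants or the core research team is not possible".

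**The concern.** The Study Setting section promises a result that the described allocation step does not by itself secure. The Discussion builds on the promise, since it counts protection against contamination between groups inside one organisation as a strength.

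With about four offices per arm, chance can load one employer onto one arm. A university and a council may differ in work pattern and in how staff respond. The article gives reason to expect this: organisational support is one of the core themes behind the intervention, and line managers deliver part of it by email. If organisation is unbalanced and absent from the model, part of an employer difference is read as an intervention effect. In the extreme case one organisation offers no comparison between arms at all. A random office effect does not repair this, because it treats offices as exchangeable whichever employer they belong to. The trial plans two-sided tests at 0.05 and is meant to inform a full trial, so the arm estimate matters even in a pilot.

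**Working it through.** The article gives no probability or balance figure on this point, so there is none to reproduce.

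**Inputs from the article.** About eight offices (Randomization); two organisations (Study Setting); model terms (Statistical Analysis).

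**Assumptions, not in the article.** Exactly eight offices, one pooled draw with four offices per arm, and a split of offices between organisations of 4/4, 3/5 or 2/6. For the size of the carry-over, offices of equal size.

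**Step 1: chance that an organisation lacks an arm.** There are C(8,4) = 70 equally likely allocations. If the smaller organisation has *a* offices and the larger *b*, the number of allocations that put *x* of the smaller one's offices in the intervention arm is C(a,x) × C(b,4−x). An arm is missing somewhere when *x* is 0 or *a*, or when 4−*x* is 0 or *b*.

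| Split | Allocations with a missing arm | Chance |
|---|---|---|
| 4/4 | C(4,0)C(4,4) + C(4,4)C(4,0) = 2 | 2/70 = 2.9% |
| 3/5 | C(3,0)C(5,4) + C(3,3)C(5,1) = 5 + 5 = 10 | 10/70 = 14.3% |
| 2/6 | C(2,0)C(6,4) + C(2,2)C(6,2) = 15 + 15 = 30 | 30/70 = 42.9% |

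The article does not state a 4:4 ratio. If each office were instead allocated independently with probability one half, the chance is 1 − (1 − 2 × 0.5^a)(1 − 2 × 0.5^b), which gives 23.4%, 29.7% and 51.6% for the same three splits.

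**Step 2: balance at the most favourable split (4/4).**

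- Exact 2:2: C(4,2) × C(4,2) = 36, so 36/70 = 51.4%.
- 3:1 in either direction: 2 × C(4,3) × C(4,1) = 32, so 32/70 = 45.7%.
- 4:0 in either direction: 2/70 = 2.9%.

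**Step 3: what a 3:1 imbalance does.** One organisation supplies 3/4 of the offices in one arm and 1/4 in the other. The difference in share is 3/4 − 1/4 = 1/2. If D is the organisation difference that remains after adjustment for the baseline value, about D/2 enters the arm contrast. The article gives no basis for a value of D.

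**Step 4: after the change.** With balanced randomisation inside each organisation, and at least two offices in each, the chance of a missing arm is 0. The number of possible allocations falls from 70 to C(4,2) × C(4,2) = 36 for a 4/4 split, or C(2,1) × C(6,3) = 40 for 2/6. Between-office degrees of freedom are about 8 − 2 = 6 without an organisation term and 5 with it. The two-sided 5% critical t rises from 2.447 to 2.571, a ratio of 2.571/2.447 = 1.05.

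**The case against.** The strongest reply is that the article is silent on stratification and does not say there was none. A separate draw per organisation would fit both the Study Setting and the Randomization text, and a journal article may leave such detail to the full protocol. This stands as far as it goes: a reader might infer that the offices were certainly drawn in one pool, or that the two sections contradict each other, and the documents show neither. It does not remove the point. If the draw was made within organisation, organisation is a stratification factor and belongs in the models, whose terms are listed without it. If it was not, the Study Setting statement is unsecured.

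Three further objections also hold in part.

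- **The size rests on assumptions.** At an even split a missing arm is unlikely (2.9%). A reader might extend the calculation to a 1/7 split and report certainty. That case should be left out, because a single office cannot hold both arms and the Study Setting statement would then fail under any allocation.
- **Baseline adjustment helps.** Every model adjusts for the baseline value, and workplace sitting is expressed as a percentage of the working day. A reader might take half of the whole organisation difference to be bias. Only the part left after adjustment carries over, mainly a difference in change or response.
- **Timing is a separate matter.** A reader might link randomisation before baseline to the missing-arm risk, but timing has no bearing on which organisation receives which arm. Participants do not learn their group until baseline is complete, so they cannot drop out before then because they know it. What stays open is staff knowledge: non-disclosure is stated for participants only, and the core team is described as unblinded. The article does not say that staff know the allocation at baseline. The scope for influence is also limited, since the primary outcome comes from a device and the questionnaires are completed online.

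**Conclusion.** The point holds in a limited form. The article states that both arms will be present at each organisation, does not describe how this is secured, and omits organisation from both mixed models. Under one pooled 4:4 draw of eight offices, the chance of a missing arm ranges from 2.9% to 42.9% over the splits considered. The more robust problem is ordinary imbalance: even at the best split, nearly half of draws (34/70 = 48.6%) are 3:1 or worse, with no model term to absorb the consequence. The size of the resulting bias cannot be given, because the residual organisation difference is unknown.

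The need for the organisation term does not depend on whether the draw was pooled; the probabilities do. This should be corrected, but it does not invalidate the trial. Staff access to the allocation before baseline is a minor, separate point.

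**What to change.** 1. In the Randomization section, state that the independent researcher randomises offices separately within each organisation. An organisation with an odd number of offices cannot be split evenly, which is a further reason for the next step.
2. In Statistical Analysis, add organisation as a fixed effect to both mixed models.
3. If allocation has already taken place, say how it was done, still add the model term, and report the number of offices by arm and organisation.
4. Separately, state that the independent researcher withholds the allocation list from the staff who collect baseline data, as well as from participants, until baseline is complete.

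The cost is a few sentences and one model term. The term uses about 1 of 6 between-office degrees of freedom, which widens intervals by about 5% through the critical value if the between-office variance is unchanged. If organisation explains some of that variance, the loss is smaller or is recovered.
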